#### 4.4. IntegNeuro™battery

The IntegNeuro™ cognitive test battery is made up of 13 different tasks which require a total of approximately 50 minutes to complete. The 13 tasks which make up the IntegNeuro™ test battery were designed and validated to challenge participants in six different cognitive domains: i) Sensori-motor; ii) Learning and memory; iii) Language; iv) Attention and working memory; v) Executive function/planning; and vi) Emotion identification [1,31,32]. Table 1 lists the specific markers which will be investigated in ACTION for cognitive and emotional function and the tasks and measures used in IntegNeuro™ to ascertain them. Each marker is a composite of up to three tasks, and have a combined sensitivity of 88% in children and adolescents with ADHD [1]. The decision to focus on the Inhibition and Emotion identification markers as primary outcomes for the ACTION study was due to recent investigations [42,51], which led us to hypothesize that these markers would be more likely to improve after non-stimulant treatment in patients with ADHD and comorbid anxiety. Research into the cognitive markers in ADHD and their response to different ADHD treatments is still in the early stages so it would be premature to limit our investigations to only two of six markers which have been validated in ADHD. Hence, all six markers will be assessed in ACTION due to the novelty of this study. Marker scores are the focal dependent measures of interest, calculated as standardized scores for the tasks each marker comprises (Table 1). More detailed scores for each individual task will also be available for secondary analyses. Williams et al. (2010) provides a clear description of the tasks which will be used in ACTION [1].

**Table 1 T1:** Six cognitive and emotional function markers, and their contributing measures

Marker	Summary definition	Task	Measure
Cognitive:			

1. Sustained attention (vigilance)	To maintain attention over time during continuous and repetitive activities.	Continuous performance task	Reaction time, total errors

2. Impulsivity	To initiate a behavior without adequate forethought; the inability to suppress automatic responses when they are inappropriate.	Continuous performance task Go-NoGo	Errors of commission Errors of commission

3. Intrusions	The repetition of erroneous responses, even in the absence of interfering stimuli.	Maze Switching of attention Verbal memory recall	Overrun errors Errors (digits and letters) Total intrusion errors

4. Inhibition	The inability to suppress task-irrelevant information.	Verbal interference	Errors (word), errors (color), errors (interference)

5. Response variability	The consistency of response time.	Continuous performance task Go-NoGo	Variability of reaction time Variability of reaction time

Emotional function:			

6. Emotion identification	The capacity to identify the facial expressions of basic emotion displayed by others.	Emotion identification task	Percentage correct, response time for each expression (fear, anger, sadness, happiness, disgust, neutral)

See Williams et al. (2010) for more detail about the tasks [1].

In the IntegNeuro™ cognitive battery, participants will hear the test instructions through a pair of headphones, and respond to the tasks by either speaking into the microphone (attached to the headphones) or using the touch-screen for non-verbal tasks. Participants will be supervised throughout the test via CCTV (closed-circuit television) from an adjacent room. Additional instructions will be given during the test if necessary. Participants will provide consent to be monitored via CCTV by signing a Surveillance Authority Form. The CCTV will only be used for the purpose of monitoring the patient during the visit and no recordings will be made.

To minimize the effect of familiarization and practice effects at subsequent testing sessions, IntegNeuro™ has a set of parallel forms for use in repeat testing sessions, whereby the sequences/words/patterns used in each of the tasks have been programmed to be different between the time-points. IntegNeuro™ will be set up to have the participant complete the test battery corresponding to their ACTION time-point.

### 5. Research endpoints

The primary endpoint will be clinically significant improvement in cognition and emotional function after ATMX treatment assessed using IntegNeuro™ (Table 1); and in ADHD symptoms (ADHD-RS IV, CGI, WPREMB, and CPRS-R subscales: Cognitive problems/inattention, Hyperactivity, Conners' ADHD index, CGI restless-impulsive, CGI total, DSM-IV inattentive, DSM-IV hyperactive-impulsive, and DSM-IV total). Further analyses will be undertaken to compare the differences in ATMX treatment effects between participants with and without comorbid anxiety; and between ADHD subtypes.

Part of the novelty of this trial lies in our utilization of objective assessments for cognition and emotional function. As such, we will also determine if our objective measures predict response to ATMX in ADHD, and in patients with comorbid anxiety. Treatment response is defined in Section 7.3.2.

The secondary endpoints will be improvements after ATMX treatment in quality of life (PedsQL - self and parent); emotional states and self-regulation (DASS-BRISC); and state and trait anxiety (CPRS-R subscales: Anxious-shy, STAI and STAIC). Previous ADHD treatment with stimulant medication and comorbid anxiety will be included as covariates.

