**Methods:**

Children and adolescents aged 6 - 17 y with ADHD will be enrolled. Clinical interview and validated scales will be used to confirm diagnosis and screen for exclusion criteria, which include concurrent stimulant use, and comorbid psychiatric or neurological conditions other than anxiety. Three assessment sessions will be conducted over the 13-week study period: Session 1 (Baseline, pre-treatment), Session 2 (six weeks, atomoxetine or placebo), and Session 3 (13 weeks, cross-over after one-week washout period). The standardized touch-screen battery, "IntegNeuro™", will be used to assess cognitive and emotional function. The primary measure of response will be symptom ratings, while quality of life will be a secondary outcome. Logistic regression will be used to determine predictors of treatment response, while repeated measures of analysis will determine any differences in effect of atomoxetine and placebo.

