#### 4.2. Baseline (Session 1), Session 2 and Session 3 measures

##### 4.2.1. ADHD symptom severity

At each testing session parents will complete the ADHD-RS IV, as a measure of ADHD symptom severity.

Parents will also rate symptom severity on the Conners' Parent Rating Scale - Revised (Long version; CPRS-R) [40]. The CPRS-R ratings will provide a second assessment of symptom severity, providing a within-study check on the consistency of symptom ratings. T-scores for all 13 subscales will be recorded, where larger T-scores indicate greater impairment.

The secondary outcomes of ACTION will be the relationships between the primary cognitive measures and ratings obtained from the ADHD-RS IV and CPRS-R.

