### 7. Statistical analysis

#### 7.1. Sample size

The data used for the power calculation of the inhibition function primary outcome measures are from a sample of 175 ADHD individuals assessed off and then on stimulant medication (methylphenidate or dexamphetamine; data not published). The power calculation of the emotional function primary outcome measures are based on a sample of 30 ADHD participants from the same sample.

Power was set at 0.9, alpha level at 0.05, and the mean difference (change in off-versus on-medication) and standard deviations for the mean of the n = 175 group was used. The means for the n = 30 group were set at '0', since there was no change expected in these outcome measures for the placebo group. After applying the pilot data means from each primary outcome measure the highest sample size estimate we obtained was n = 152 for each group under two-tailed conditions. Therefore, a minimum total of 152 participants are required in this cross-over study to achieve the desired level of probability in detecting a statistically significant difference across the two primary outcome measures.

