#### 7.3. Data analysis

The ACTION study will adopt an all available data analytical approach, meaning that all data obtained will be included in analyses, regardless of adherence to the study. Accordingly, there will be no imputation of missing data. For all analyses, a *p *value of <0.05 will be considered statistically significant.

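### Two markers are named and powered as primary, but Section 5 lists 17 primary measures, all tested at p<0.05 with no stated rule for success

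*Protocol article*

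**What the plan says.** Section 4.4 refers to "The decision to focus on the Inhibition and Emotion identification markers as primary outcomes for the ACTION study" and explains why those two were chosen, while keeping all six markers under assessment. Section 7.1 follows that choice: "Power was set at 0.9, alpha level at 0.05", then "the highest sample size estimate we obtained was n = 152 for each group under two-tailed conditions". It concludes that 152 participants in total are enough for "detecting a statistically significant difference across the two primary outcome measures".

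Section 5 is wider: "The primary endpoint will be clinically significant improvement in cognition and emotional function after ATMX treatment". It points to Table 1, which has six markers. The same sentence adds ADHD symptoms, measured by ADHD-RS IV, CGI, WPREMB and eight named CPRS-R subscales.

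Two further places pull in other directions. Section 4.3, which contains CGI and WPREMB-R, is introduced as serving the secondary aims. Section 7.3.2 ties response on the primary outcome to an improvement of at least 25% in ADHD-RS IV and CPRS-R scores, with a later cut-point of 40%.

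Section 7.3 then states, for all analyses, that a p "value of <0.05 will be considered statistically significant". The article gives no adjustment, no testing order and no rule that one or all measures must succeed.

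**The concern.** A reader cannot tell from the article what result would make the trial positive. Under Sections 4.4 and 7.1, no effect on either marker means that the primary objective failed. Under Section 5, the same data could be presented as a primary finding on a symptom subscale. Two things are at stake. The false-positive rate attached to a primary claim depends on a success rule that is not given. And the stated power belongs to a different and much smaller set of outcomes than the one Section 5 calls primary. If the set is settled only after the data are unblinded, the choice could follow the results.

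**Working it through.** **1. Counting the Section 5 endpoint.** Six Table 1 markers + three scales (ADHD-RS IV, CGI, WPREMB) + eight CPRS-R subscales = 17 measures, against two in Sections 4.4 and 7.1.

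**2. The plan's own figure.** Inputs from Section 7.1: power 0.90, two-sided alpha 0.05, n = 152. No mean difference or SD is given, so 152 cannot be reproduced, only inverted. With z(0.975) + z(0.90) = 1.960 + 1.282 = 3.242:
- read as 152 per group: d = 3.242 × √(2/152) = 0.372;
- read as 152 pairs: within-person standardized difference = 3.242/√152 = 0.263.

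The calculation uses the full 0.05, with no split between the two outcomes.

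**3. Chance of at least one false positive**, one atomoxetine-versus-placebo test per measure, each at two-sided 0.05. If independent, this is 1 − 0.95^k: 0.0975 for k = 2 and 0.582 for k = 17. Counting improvements only, it is 1 − 0.975^k: 0.049 and 0.350. The documents give no correlations, so a common correlation was assumed and simulated with normal test statistics (400,000 draws):

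| Assumed correlation | 2 measures, two-sided | 17 measures, two-sided | 17 measures, improvements only |
|---|---|---|---|
| 0 | 9.8% | 58% | 35% |
| 0.3 | 9.5% | 49% | 25% |
| 0.5 | 9.1% | 39% | 19% |
| 0.7 | 8.4% | 27% | 14% |
| 0.9 | 7.0% | 15% | 7% |

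For comparison, a single test gives 5% two-sided, or 2.5% counting improvements only. With assumed blocks (markers correlated 0.2 to 0.5, symptom scales 0.6 to 0.8, blocks independent), 17 measures give 35% to 45% two-sided.

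**4. Power at 152 once error is controlled.** Holding the implied effect fixed, power = Φ(3.242 − z(1 − α/2)). At α = 0.05 this returns the plan's 90%.
- Two measures, α = 0.025: Φ(3.242 − 2.241) = 84.1%. Keeping 90% needs 152 × ((2.241 + 1.282)/3.242)² ≈ 180.
- 17 measures, α = 0.05/17 = 0.00294: 60.6%. Keeping 90% needs 262.
- Both of two required, each at 0.05: 0.90 × 0.90 = 81% if independent with 90% each. Keeping 90% needs about 187.

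**5. What pairing could add.** If 152 came from a two-group formula with d = 0.372, the within-person standardized difference is 0.372/√(2(1 − ρ)). At α = 0.025 and 152 participants, power is 84% for ρ = 0, 92% for ρ = 0.2 and 99% for ρ = 0.5. If 152 was already a number of pairs, it stays at 84%.

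**The case against.** The strongest reply is that Section 5 joins cognition and symptoms with a plain conjunction and never says that one significant measure is enough. That is right. A reader might infer that any of the 17 may be reported as the primary result and that the error rate is therefore 58%. The article does not say so. If all 17 had to succeed, type I error would be controlled and the difficulty would be power, for which Section 7.1 does not size. The 58% also needs independence, which is implausible: the list sets DSM-IV total beside its inattentive and hyperactive-impulsive parts, and CGI total beside CGI restless-impulsive. Since the endpoint is improvement, the one-direction figures are a fair alternative.

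Three other tempting readings go too far.
- The abstract says "The primary measure of response will be symptom ratings, while quality of life will be a secondary outcome". This looks like a rival primary endpoint, but response is a term that Section 7.3.2 defines for the prediction models, so the sentence need not rank endpoints.
- Section 4.2.1 says "The secondary outcomes of ACTION will be the relationships between the primary cognitive measures and ratings". This makes the relationship secondary. It does not rank the symptom ratings themselves.
- Three contrasts in Section 7.3.3 times 17 measures suggests 51 tests. CGI Improvement is rated only at Sessions 2 and 3, and WPREMB-R only during the treatment phases, so neither has a baseline contrast. Only atomoxetine versus placebo is the randomized comparison.

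It may also be said that multiplicity belongs in an analysis plan that is not shown. The detailed procedure can. But the article itself states conflicting primary sets and a blanket 0.05, and a later plan would have to overrule one of its sections to be coherent.

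**Conclusion.** The contradiction stands and concerns what counts as success. Sections 4.4 and 7.1 give two primary outcomes, and Section 5 gives 17. Sections 4.3 and 7.3.2 do not fit either set cleanly. Section 7.3 fixes an unadjusted 0.05, and no success rule is stated. The 90% power therefore does not apply to the Section 5 endpoint.

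The size of the error inflation is conditional. If any one measure may count, it is about 15% to 58% two-sided over 17 measures, or 7% to 35% counting improvements only, for assumed common correlations from 0.9 to 0. Even the narrow reading, two markers each at 0.05 with either sufficient, gives 7% to 10% two-sided. None of these is the trial's known error rate, because neither the rule nor the correlations are documented.

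**What to change.** Before unblinding, and by a dated amendment:

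- Name Inhibition and Emotion identification, compared between atomoxetine and placebo, as the only primary outcomes, since the trial was sized on them.
- State one rule that controls error, for example Holm at an overall two-sided 0.05. Requiring both markers, or testing them in a fixed order, would also control it. The sponsor should choose and say which.
- Make the other four markers, ADHD-RS IV, CGI, WPREMB-R and the CPRS-R subscales secondary, reported with confidence intervals and without confirmatory claims.
- Align the abstract and Sections 4.3, 5, 7.3 and 7.3.2 with that choice.

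**Cost.** No planned measurement or analysis is lost. Enrolment began in March 2008 and Section 2.5 requires each IRB to approve modifications, so this is more than an edit of wording, and the amendment should record that the choice was made blinded. Power should be restated: at 152 participants, with the effect implied by the stated sample size, it is about 84% at the first Holm step instead of 90%, and about 180 participants would restore 90%. It would be higher only if 152 came from a two-group formula and the within-person correlation is positive (about 92% at 0.2 and 99% at 0.5, both assumed). The fix should not be presented as free of cost on the strength of the higher figure.

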### 6. Adverse events and safety monitoring

Parents are advised to contact the CTC in the case of any adverse events - defined as any physical, behavioral/psychological, or physiological problems potentially related to the study treatment or testing sessions. In the case of mild adverse reactions, the parent will be asked to continue on the study treatment and monitor the condition, informing the CTC if the problem persists or worsens. The study clinician will also be available for the CTC to obtain a sound medical opinion if required. If the adverse reaction is deemed an emergency, the parents will be advised to take the participant to the Emergency department of their nearest hospital. In these situations, the participant's group allocation will be revealed in order to inform the hospital of what the participant was administered. All adverse events will be recorded.

The investigators will be responsible for monitoring the safety of study participants and to take appropriate action concerning any event that seems unusual. They will ensure that appropriate medical care is maintained throughout the study and after the study to follow adverse events.

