**Figure 2 F2:**
[figure not shown]
**Atomoxetine dosage schedule**. Week 1 is the initiation dose, with approximately 0.5 mg.kg^-1 ^for each patient group; weeks 2-6 reach the target dose of approximately 1.2 mg.kg^-1 ^for each group (with minimum dose of 1.0 mg.kg^-1 ^and maximum dose of 1.4 mg.kg^-1^).

Randomization will be performed by a hospital biostatistician using a centralized, pre-determined pair-wise randomization technique, ensuring an even allocation of participants to receiving ATMX or placebo first; while also taking into account the expected ratios across the five weight groups (Figure 2). Once the randomization list has been generated, the hospital biostatistician will forward a copy of the master list to the compounding chemist responsible for packaging and labeling the blister cards for the study. The investigators, referring clinicians, and the participants will remain blinded to group allocation. All capsule packages will be prepared prior to the commencement of the trial, and packages will be dispensed according to the pre-determined randomization master list. As each participant enters the study, they will be allocated a study ID code in the order of numerical sequence. The corresponding blister cards will be labeled with the ID codes and corresponding study phase only. The participating clinicians, investigators, and the participants will be blinded to group allocation until the completion of the study.

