#### 2.3. Session 2 (6 weeks; post-Phase A)

The assessments undertaken at Baseline (Session 1) will be repeated at Session 2. Parents will be reminded to return their child's capsule blister packs and "Take Home Package" booklet, so that the investigators can record compliance to the study drugs during each study phase. As with Session 1, on completion of Session 2 parents will be provided with their child's next course of study capsules and a second "Take Home Package" booklet for use during Phase B of the study.

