#### 2.5. Ethical considerations

The ACTION study will be conducted according to the principles of the Declaration of Helsinki 2008, and International Conference on Harmonization (ICH) guidelines. Investigators ensure that "Good Clinical Practice" principles will be adhered to, as outlined in 21 FDA Code of Federal Regulations CFR 312, subpart D, "Responsibilities of Sponsors and Investigators," 21 CFR, part 50, 1998, and 21 CFR, part 56, 1998.

Institutional Review Board (IRB) approval is obtained prior to patient enrolment at any clinical site. All protocol modifications will be submitted to each IRB for approval before implementation. Prior to undertaking any study-related procedures, investigators will obtain written informed consent from each study participant after verbal and written explanation of study aims, methods, and potential hazards and benefits.

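### Section 6 makes possible relatedness part of the adverse event definition and describes only parent-initiated reporting, so all-cause events may be under-recorded in both phases

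*Protocol article*

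**What the plan says.** Section 6 of the protocol article sets out the reporting route and the definition in one sentence. "Parents are advised to contact the CTC in the case of any adverse events", and these are "defined as any physical, behavioral/psychological, or physiological problems potentially related to the study treatment or testing sessions". Where a reaction is mild, "the parent will be asked to continue on the study treatment and monitor the condition, informing the CTC if the problem persists or worsens". Medical advice from the study clinician is available to the CTC. The first paragraph closes with "All adverse events will be recorded".

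The second paragraph adds a general duty: "The investigators will be responsible for monitoring the safety of study participants and to take appropriate action concerning any event that seems unusual".

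On blinding, the text under Figure 2 in Section 1 says: "The participating clinicians, investigators, and the participants will be blinded to group allocation until the completion of the study". Section 6 allows the allocation to be revealed in an emergency.

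The endpoints (Section 5) and the analyses (Section 7.3) name no safety endpoint and no comparison of adverse events between atomoxetine and placebo.

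**The concern.** Whether something happened and whether the treatment caused it are separate questions. Section 6 merges them: a problem counts as an adverse event only if it may be related to the treatment or the testing. Because the definition sits inside the instruction to parents, a lay person makes the first causal judgement before anyone in the trial hears of the problem.

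This matters here because Section 6 counts behavioural and psychological problems as adverse events, while the participants are children with ADHD, some with comorbid anxiety. New irritability, low mood or restlessness is easily read as part of the existing condition. A blinded placebo phase makes it possible to see which events occur more often on drug without anyone judging cause, but only if events are recorded whatever their apparent cause. An event that was never recorded cannot be recovered later: Section 7.3 analyses the data obtained and imputes nothing.

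**Working it through.** The article states no adverse event rate, reporting fraction or safety sample size, so there is no figure of its own to reproduce. The check is a reading of Section 6, followed by an illustration with assumed rates.

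**Does anything in Section 6 remove the filter?**

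1. The promise to record all adverse events uses the term just defined. A problem judged unrelated is not an adverse event in that sense, so the promise does not reach it.
2. The investigators' duty has no relatedness condition, but it concerns events that strike them as unusual. That is another judgement, and no means of learning of such events is described beyond the parent's contact.
3. The section moves from the term event to the term reaction for the same reports, which again treats occurrence and cause as one.
4. The mood and symptom scales (Sections 4.2 and 4.3) are completed whatever the parent believes about cause. They yield scores, not events with an onset and an outcome, so they soften the loss without replacing event records.

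The filter therefore stands as written.

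**What could it do to the counts?**

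Inputs: 152 children per phase, the minimum in Section 7.1, which was set for the cognitive and emotional outcomes and not for safety. True event rates and capture fractions are assumptions.

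Formulas: observed rate = true rate × capture fraction; RD = difference of observed rates (atomoxetine minus placebo); RR = their ratio.

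*Counts, assumed true rates 20% and 10%, equal capture:*
- Full capture: 152 × 0.20 = 30.4 and 152 × 0.10 = 15.2.
- 30% capture: 30.4 × 0.30 = 9.1 and 15.2 × 0.30 = 4.6.
- 60% capture: 30.4 × 0.60 = 18.2 and 15.2 × 0.60 = 9.1.

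*Contrast between phases:*

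| Assumed true rates | Capture, atomoxetine / placebo | Observed rates | RD | RR |
|---|---|---|---|---|
| 40% / 25% | 100% / 100% | 0.40 / 0.25 | 0.15 | 1.60 |
| 40% / 25% | 50% / 50% | 0.20 / 0.125 | 0.075 | 1.60 |
| 40% / 25% | 80% / 50% | 0.32 / 0.125 | 0.195 | 2.56 |
| 40% / 25% | 50% / 80% | 0.20 / 0.20 | 0.00 | 1.00 |
| 20% / 10% | 100% / 100% | 0.20 / 0.10 | 0.10 | 2.00 |
| 20% / 10% | 50% / 50% | 0.10 / 0.05 | 0.05 | 2.00 |
| 20% / 10% | 80% / 50% | 0.16 / 0.05 | 0.11 | 3.20 |
| 20% / 10% | 50% / 80% | 0.10 / 0.08 | 0.02 | 1.25 |

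With equal capture the ratio is preserved, but counts and precision fall. At 40% versus 25%, halving capture takes the power of a simple two-proportion comparison from 0.80 to 0.425, treating the phases as independent, which is only an approximation in a cross-over. With unequal capture the difference can be inflated or erased. The article gives no basis for choosing among these rows.

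**The case against.** The best reply is that the threshold is low and the article is a summary. Potential relatedness is a broad test, and testing sessions are covered as well as treatment. A mood change during dosing that a parent blames on school is still potentially related, so the definition itself need not exclude it. This is fair, and it limits the point to events that *may* go unrecorded. It does not remove it, because the parent still decides in practice whether the test is met.

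Four stronger readings are tempting, and the document does not support them:

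- **Parent contact is the only way an event is captured.** It is the only reporting route described. The article does not call it exclusive, and it gives investigators a monitoring duty of their own.
- **No one asks about adverse events at the visits.** No enquiry is listed for Sessions 1 to 3, but those lists are incomplete: the Figure 1 legend omits the STAI/STAIC, which Section 4.2.2 uses at all three sessions. A condensed article may leave visit-level questioning to the full protocol, so its absence is not a finding.
- **The planned safety comparison is biased.** None is stated. Nor is unequal reporting between phases shown: the capsules look identical, and participants, clinicians and investigators are blinded.
- **Section 6 breaches the commitment in Section 2.5.** That section cites "International Conference on Harmonization (ICH) guidelines" but reproduces no adverse event definition from them, so a conflict cannot be shown from this document.

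**Conclusion.** The point holds in a limited form. Section 6 states, and does not merely leave open, that potential relatedness is part of what makes a problem an adverse event, and its described route starts with the parent. Followed as written, it can under-record all-cause events in both phases. That conclusion assumes only that some parents will not report problems they attribute to something else.

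The size of the loss, and the direction of any bias between phases, cannot be determined from the document; every rate and capture fraction in the illustration is assumed. This is a moderate safety-reporting weakness in a placebo-controlled drug trial in children and adolescents. It does not touch the stated efficacy endpoints or analyses. It should be corrected because the loss is permanent and the remedy is cheap.

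**What to change.** Reword the definition in Section 6 so that an adverse event is any untoward physical, behavioural/psychological or physiological occurrence from the first study procedure onward, whether or not it is thought related. The start should be Session 1 testing and not the first capsule; otherwise problems arising from baseline testing, which the present wording covers, would drop out.

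Then:
- record the onset date and study phase of each event;
- have a blinded clinician judge relatedness as a separate item;
- tabulate all events by atomoxetine and placebo phase, whatever the relatedness judgement.

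An open question to parent and child at the existing Sessions 2 and 3 would support this, if the full protocol does not already include one.

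The cost is one reworded definition, a few fields on the event form, a short judgement per event and one table, with no extra visit. The small downside is that more unrelated minor events will be recorded.
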